# Implementation of a Comprehensive and Personalised Approach for Older People with Psychosocial Frailty in Valencia (Spain): Study Protocol for a Pre–Post Controlled Trial

**DOI:** 10.3390/ijerph21060715

**Published:** 2024-05-31

**Keywords:** integrated care, personalised care, psychosocial frailty, older people, pre–post controlled clinical trial

## Abstract

With ageing, the risk of frailty increases, becoming a common condition that exposes older people to an increased risk of multiple adverse health outcomes. In Valencia (Spain), the ValueCare project develops and applies a value-based care approach that addresses the multidimensional nature of frailty by implementing integrated and personalized care to tackle psychosocial frailty. A pre–post controlled design with a baseline measurement at inclusion, at the end of implementation and a follow-up measurement after 6 months of intervention. In Valencia (Spain), 120 participants over 65 years of age are recruited from primary care centres to receive the ValueCare comprehensive and personalised care plan according to the results and are compared with 120 participants receiving “usual care”. An assessment questionnaire is designed using validated instruments, and a personalised care plan is developed specifically for each participant based on the results obtained. The study protocol has been registered under the ISRCTN registration number ISRCTN25089186. Addressing frailty as a multidimensional and multifactorial risk condition requires the development and implementation of comprehensive assessments and care. In this context, this study will provide new insights into the feasibility and effectiveness of a value-based methodology for integrated care supported by ICT for older people experiencing frailty.

## 1. Introduction

The ageing of the world’s population is indeed a complex and multifaceted phenomenon with both positive and challenging aspects. An ageing population can have far-reaching socioeconomic consequences, for instance, on the care system due to increases in public spending on health and social care [1,2]. As people age, they are at increased risk for chronic diseases, functional impairments, and frailty [3,4,5]. Frailty is indeed considered one of the most problematic expressions of ageing, constituting a risk factor for falls, loss of mobility, cognitive impairment, disability, dementia, hospital admissions, cardiovascular diseases, loneliness, and even mortality [6,7,8]. Research examining the relationship between frailty and loneliness has found strong associations between these two factors, and it suggests a bidirectional relationship [9,10]. Recent studies have confirmed that frail, older people have smaller social networks and higher levels of loneliness [11,12]. Likewise, older people who experience high levels of loneliness have an increased risk of becoming physically frail or prefrail [13]. Similar to frailty, loneliness has also been observed to be closely associated with different negative health outcomes, such as cardiovascular disease, disability, cognitive impairments, depression, disability, and mortality [10,14,15].

In terms of prevalence, in Europe and, in particular, Spain, there is no consensus on the prevalence of frailty. Although studies have confirmed that frailty increases with age and is more frequent in women than in men [16,17,18,19], there are notable variations, depending on the assessment tools, in population variability in terms of geographical location, socioeconomic status, gender, and the presence of chronic diseases [19,20]. A recent study showed that >50% of the population over 50 years of age in Europe is pre-frail/frail, with the overall prevalence of pre-frailty being 42.9% and of frailty 7.7% [20]. In Spain, the most recent studies have shown a prevalence of frailty higher than 25% for the population aged 70 years and older, with significant differences according to geographical areas and being twice as high in women as in men [17,18].

Another issue when studying frailty is that the physical frailty phenotype has received significant attention in the literature, and it is often the most prominent aspect of frailty discussed [21]. However, it is important to note that frailty is a multidimensional concept, and there are other dimensions of frailty that are equally important but may not receive as much attention in the literature. These dimensions include the psychological and social aspects of frailty [22].

In recent years, there has been a growing interest in expanding the understanding of frailty to include these other dimensions and develop more comprehensive and a more holistic approach to managing and preventing frailty and its associated adverse health outcomes. Moreover, the bidirectional relationship between loneliness and frailty, coupled with the multidimensional nature of both constructs, underscores the need for comprehensive strategies to address these issues in older adults [23]. In this sense, the implementation of value-based healthcare principles in the context of frailty lies in addressing frailty from an integrative perspective, reorganising care around patients in an effective and efficient manner supported by digital health solutions [24]. Concretely, among the key principles of value-based care are individualized care plans, shared decision-making, holistic assessments including measurable outcomes, the provision of integrated services, and early interventions. All of these aspects of the value-based care model are essential to addressing the complex interplay of frailty, depression, and social support in older adults [25]. The adoption of value-based care in addressing these conditions among older adults leads to improved health indicators, such as reduced hospitalisations, better mental and physical health, enhanced quality of life, and lower healthcare costs. By focusing on patient-centred, comprehensive, and coordinated care, VBC transforms the healthcare experience for older adults and yields measurable health benefits [26,27].

The literature has shown that social participation is key when developing comprehensive strategies to address frailty, especially frailty understood as a holistic concept including social and psychological aspects [28]. Social participation has been proven to effectively address psychological and social frailty and loneliness [29]. In particular, when developing interventions, it is essential to address the individual dimension, taking into account the individuality of each person, favouring empowerment, and allowing them to manage their own loneliness [14]. In this sense, the literature suggests the need to educate the population about actively investing in their social supports (family and friends) and also emphasises the great importance of boosting the person’s own motivation to actively change their situation [30].

In this regard, the motivational interview technique may be presented as a useful tool to support intervention strategies focused on improving intrinsic motivation and behavioural change among older adults experiencing frailty. Motivational interviewing is a counselling approach developed to help individuals find motivation within themselves to make positive behavioural change [31]. The core principle of motivational interviewing involves engaging in a collaborative conversation with individuals to explore and resolve their ambivalence toward change. Therefore, motivational interviewing may be used for supporting individuals in planning their personal objectives, boosting their motivation, and moving forward with behavioural change that may lead to improved frailty status and loneliness feelings.

This study is framed within the ValueCare project—*Value-based methodology for integrated care supported by ICT*—a research project funded by the European Commission under the Horizon 2020 programme. This project conforms a consortium of 17 partners from 8 European countries. The aim of the ValueCare project is to provide efficient and outcome-based integrated (health and social) care to the population aged ≥65 experiencing frailty, cognitive impairment, and/or multiple chronic conditions, with the objective of improving their quality of life by applying value-based methodologies supported by digital solutions. In this project, study sites in seven European countries are implementing and validating the ValueCare intervention: Valencia in Spain, Rijeka in Croatia, Athens in Greece, Cork/Kerry in Ireland, Coimbra in Portugal, and Rotterdam in the Netherlands. In each of these sites, the ValueCare intervention is aimed to address a specific health condition. In this particular study, the Spanish intervention focused on frailty is presented.

### Objectives

The aim of this study is to evaluate the ValueCare approach implemented in the pilot of Valencia (Spain), whose intervention is based on motivational interviewing, supported by a digital tool, to encourage behavioural change towards greater social engagement and healthier living. This study, using a pre–post controlled design with a study sample of 240 older adults experiencing frailty (120 individuals in the intervention group and 120 in the comparison group), specifically addressed the benefits for older people experiencing psychosocial frailty to be able to evaluate implementation outcomes. We intend to accomplish this objective through the following specific objectives:(a)To compare the benefits of the ValueCare intervention deployed in the Valencia pilot vs. usual care for older people in terms of frailty, loneliness, social support, health-related quality of life, and healthy lifestyle behaviour.(b)To evaluate the benefits of the ValueCare approach deployed in the Valencia pilot centre in terms of reducing the use of outpatient and inpatient health and social care among older people.(c)To evaluate the satisfaction of the target population with the ValueCare intervention deployed in the Valencia pilot centre.

## 2. Materials and Methods

### 2.1. Design

An experimental design involving both intervention and comparison groups will be employed in a controlled pre–post study, aiming to investigate the effects of the intervention by comparing outcomes between the two groups before and after the intervention period.

### 2.2. Study Participants: Inclusion and Exclusion Criteria

The study sample was composed of 240 older adults experiencing frailty (120 individuals in the intervention group and 120 in the comparison group). Participants were randomly assigned to each of the groups. Expecting a 20% loss to follow-up between T0 and T1 (e.g., due to mortality, rehousing, or study withdrawal), we expected to obtain complete data from 96 participants in the intervention group and 96 participants in the control group of each large-scale pilot site (in *n* = 192 study participants with complete data at follow up, equally divided over the intervention group and the control group). We assumed equal standard deviations in the intervention group and the control group, an alpha level of 0.05, and a power of 0.80. For this expected overall sample size and assumptions, with regard to the continuous outcome measures, a difference of 0.23 SD (standard deviation) between the intervention group and the control group can be detected at follow-up.

Participants in the intervention group engaged in a 12-month intervention phase tailored to their needs, receiving a personalised care plan agreed through a shared decision-making process, whereas those in the comparison group maintained their usual care. All participants were evaluated at baseline, after 12 months, and after 18 months.

The inclusion criteria encompassed individuals aged 65 or above, experiencing frailty, residing independently within the community, and affiliated with one of the seven healthcare centres under the Malvarrosa-Clinic Health Department within the Valencia study area. The exclusion criteria involved individuals with cognitive impairments, significant dependency, institutionalisation, inability to provide informed consent, or lack of proficiency in the Spanish language.

Patients who met the inclusion criteria were invited to participate in the ValueCare project, where a comprehensive explanation of their involvement in the project was provided. Patients interested in participating in this study were requested to sign the informed consent form, indicating their voluntary, informed, and explicit consent to participate in this study and permit the processing of their data.

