### 2.3. Recruitment and Randomization

The recruitment of the study participants was carried out by social and healthcare professionals from seven participating healthcare centres: Alfahuir Health Centre, Salvador Pau Health Centre, Benimaclet Health Centre, Serrería I Health Centre, Salvador Pau Allende Health Centre, República Argentina Health Centre, and Chile Health Centre. All of these centres belong to the Malvarosa-Clinic Health Department in the city of Valencia.

The general practitioners, who are familiar with their patient’s clinical record, contacted them to ensure that these individuals met the inclusion criteria mentioned above, ensuring their potential eligibility as participants. Once included, participants were requested to complete the baseline assessment. Following the completion of the baseline questionnaire, the allocation of study participants into either the intervention or control group occurred through a randomization procedure. To ensure the concealment of the randomisation sequence, the Oxford Minimization and Randomization (OxMaR) system was employed. This computer-based centralised method ensures proven security measures to prevent bias in the sequence [32]. For safeguarding personal information, every participant was assigned an identification code that corresponds to their group and the specific healthcare centre with which they are affiliated.

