Apart from the motivational sessions with social and healthcare professionals, participants are able to engage in social workshops organized on a monthly basis in each of the health centres participating in the study. These workshops offer opportunities for interaction among participants within the intervention group. Additionally, communication will be facilitated through WhatsApp groups and the dedicated ValueCare APP, allowing further interaction and engagement among participants. In this way, face-to-face relationships are strengthened through information and communication technologies, doubly favouring the active participation of older people in the community, reducing social frailty and improving mental well-being [41].

Specifically, the ValueCare application (Vodafone Innovus, Athens, Greece) [42] is a mobile application with which the participants of the intervention group will be able to interact and through which the achievement of the prescribed goals will be encouraged and healthy lifestyles will be promoted. To ensure that the ValueCare digital solution is adapted to the local context as well as to the needs and interests of older people, informal caregivers, managers, policy-makers, ICT experts, and health and social practitioners, strategies based on collaborative approaches such as co-design are implemented. In this sense, co-design is paramount to providing integrated person-centred care, as it allows for the involvement of all stakeholders in the development of digital health solutions [43]. A total of 2 rounds of co-design were implemented before the ValueCare implementation phase with 212 participants. All co-design rounds included focus group sessions to explore the opinions, perceptions, preferences, and experiences of the target groups around the ValueCare concept and ValueCare solution. A more generic first round aims to define the value-based model and the digital solution to build the concept and the digital solution according to the needs of all stakeholders, presenting and discussing the added value of the value-based concept in today’s society. The second, more specific co-design round aims to define the technical features and properties of the ValueCare solution as well as its involvement and interaction during the implementation phase of the intervention.

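### The detectable difference in section 2.2 makes no allowance for centre-based group delivery in the intervention arm, so power is below the independence figure at any positive intraclass correlation

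*Protocol article*

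**What the plan says.** All quotations are from the protocol article.

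- **Unit of randomisation (section 2.3).** Participants are randomised one by one after baseline: "the allocation of study participants into either the intervention or control group occurred through a randomization procedure". They come from seven health centres, and the identification code records both group and centre.
- **Sizing (section 2.2).** The numbers are "120 individuals in the intervention group and 120 in the comparison group". The plan continues "Expecting a 20% loss to follow-up between T0 and T1", and then "we expected to obtain complete data from 96 participants in the intervention group and 96 participants in the control group". The remaining inputs are in one sentence: "We assumed equal standard deviations in the intervention group and the control group, an alpha level of 0.05, and a power of 0.80". The conclusion drawn is that "a difference of 0.23 SD (standard deviation) between the intervention group and the control group can be detected at follow-up".
- **Group component (section 2.5).** Besides monthly motivational meetings with the professionals following them, intervention participants may attend "social workshops organized on a monthly basis in each of the health centres participating in the study". The purpose is explicit: "These workshops offer opportunities for interaction among participants within the intervention group". WhatsApp groups and an app support further contact. The section credits this contact with reducing social frailty and improving mental well-being.
- **Control arm (section 2.6).** Controls receive usual care when they need it, with no group activity.

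The article gives no ICC, design effect or analysis model.

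**The concern.** When people in one arm are treated together and are meant to influence one another, their outcomes tend to become alike within groups. Individual randomisation does not prevent this, because the similarity arises after allocation. Here it would arise in the intervention arm only.

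The inputs listed in section 2.2 are those of a comparison of 192 independent people. If intervention outcomes are positively correlated within centre groups, the variance of the between-arm difference is larger than that calculation allows. The detectable difference is then larger, and the power at any given difference smaller. The main outcome (PROMIS-10) is affected. Loneliness and psychosocial frailty are likely to be affected most, since shared social activity acts on them directly.

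This is more than a detail that an analysis plan might hold. The article publishes a numerical detectable difference, and the assumptions listed for it do not match the delivery described three sections later.

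**Working it through.** **Inputs from the article:** 120 per arm; 20% loss, so 120 × 0.80 = 96 per arm; equal SDs; alpha 0.05 (sidedness not stated, two-sided taken); power 0.80; seven centres.

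**Assumptions, not in the article:** intervention completers spread evenly over seven centre groups, m = 96/7 = 13.7; total SD of 1 in both arms; no delivery-related grouping among controls; ICC from 0.01 to 0.10.

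**Step 1. The plan's own figure under independence.**
Detectable difference = (1.960 + 0.842) × √(2/96) = 2.802 × 0.1443 = 0.404 SD (0.406 with the t distribution). One-sided, it is 0.359 SD. The stated 0.23 SD is not reproduced. It would need 297 per arm (234 one-sided), and with 96 per arm it has 35.7% power (48.0% one-sided). Baseline adjustment would reach 0.23 SD only with a baseline to follow-up correlation of about 0.82, which the article does not state. The grouping effect is therefore measured from 0.404 SD, the difference that the stated inputs support.

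**Step 2. Grouping in the intervention arm only.**
- Design effect in that arm: DE = 1 + (13.7 − 1) × ICC = 1 + 12.7 × ICC.
- Standard error of the difference: √((1 + DE)/96).
- Detectable difference: 2.802 × that standard error.
- Power at 0.404 SD: Φ(0.404/SE − 1.960).
- Type I error of a test that ignores the grouping: 2 × [1 − Φ(1.960 × √(2/(1 + DE)))].

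Example at ICC 0.05: DE = 1 + 12.7 × 0.05 = 1.636; SE = √(2.636/96) = 0.1657; detectable difference = 2.802 × 0.1657 = 0.464; power = Φ(2.44 − 1.96) = 68.5%.

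| ICC (assumed) | DE | Detectable difference (SD) | Power at 0.404 SD | Type I error if grouping is ignored |
|---|---|---|---|---|
| 0 | 1.00 | 0.404 | 80.0% | 5.0% |
| 0.01 | 1.13 | 0.417 | 77.5% | 5.7% |
| 0.02 | 1.25 | 0.429 | 75.1% | 6.5% |
| 0.05 | 1.64 | 0.464 | 68.5% | 8.8% |
| 0.10 | 2.27 | 0.517 | 59.1% | 12.5% |

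Starting from 0.406 instead of 0.404 gives 0.467 at ICC 0.05. A simulation of the ordinary t-test (20,000 runs per ICC, groups of 13 or 14) gave type I errors of 6.1%, 6.6%, 8.7% and 12.9% at the four positive ICCs, in line with the last column. The normal approximation ignores the few degrees of freedom that seven groups provide. A simulated group-mean test had 77% power at 0.406 SD even at ICC 0, so a real analysis may do somewhat worse than the table.

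**Step 3. What baseline adjustment can recover.**
Assume a correlation of 0.5 between T0 and follow-up, and ICC 0.05. Adjustment reduces the total variance to 1 − 0.25 = 0.75. The between-group part of 0.05 arises after randomisation, so T0 cannot remove it. The residual ICC becomes 0.05/0.75 = 0.067 and DE = 1 + 12.7 × 0.067 = 1.85. Detectable difference = 2.802 × √(0.75 × (1 + 1.85)/96) = 0.42 SD. Multiplying 0.467 by √0.75 to get 0.40 SD would wrongly shrink the group variance as well.

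**The case against.** The strongest objections, and what stands of each:

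- **The grouping may be weak.** Workshops are available rather than compulsory, the core of the intervention is individual motivational interviewing, and the WhatsApp groups are not said to be formed by centre. Neither the number of professionals nor their link to centres is given. This stands. It makes the low end of the ICC range more likely, where the loss is about 2.5 to 5 percentage points of power. It does not bring the loss to zero.
- **Error control depends on the analysis.** A reader might infer that the trial's 5% error rate fails. The article does not support that. It states no analysis model, and an analysis plan not shown here may handle the grouping. The last column of the table applies only if the grouping is ignored.
- **The stated power already fails for another reason.** A reader might also infer that grouping is why 80% power is not reached. It is not the main reason: at 0.23 SD, power is 35.7% with no grouping, and grouping at ICC 0.05 takes it only to 28.4%. The two errors are separate. Correcting 0.23 to about 0.41 SD would still leave a figure too favourable for this design.
- **Controls attend the same centres.** Pre-existing centre differences are shared by both arms and cancel so far as allocation is balanced within centre. The design effect above covers only the similarity created by delivery in the intervention arm. That controls have none is an assumption, though one that fits usual care.

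**Conclusion.** The point holds in this limited form. The article describes an individually randomised trial with group delivery in one arm, and the inputs it lists for the detectable difference treat all 192 completers as independent. At any positive intervention-arm ICC, power is below the independence figure. Over assumed ICCs of 0.01 to 0.10, the detectable difference is 0.417 to 0.517 SD instead of 0.404 SD, and power at 0.404 SD is 77.5% to 59.1% instead of 80%. The loss is modest at the lower ICCs, which are the more likely ones, and material from about 0.05 upwards.

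These sizes rest on an ICC range that the documents do not supply, on an even spread over seven centre groups, and on a normal approximation. That the sizing inputs contain no allowance for grouping is read directly from section 2.2 and needs none of these assumptions.

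**What to change.** Keep the sample size.

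1. In section 2.2, restate the detectable difference with an intervention-arm design effect of 1 + 12.7 × ICC, over a stated ICC range with its justification. Do this together with correcting 0.23 SD or stating the assumption that produces it.
2. In the analysis plan, specify for the between-arm comparison a model adjusted for the T0 value of the outcome, with a random health-centre effect in the intervention arm only, residual variances that may differ by arm, and small-sample degrees of freedom (Satterthwaite or Kenward-Roger). If the plan already does this, a cross-reference is enough.
3. If a gain from baseline adjustment is claimed, state the assumed correlation and apply it to the individual-level variance only. With 0.5, the figure at ICC 0.05 is about 0.42 SD.

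The cost is wording. T0 values are already collected and the identification code already records centre, so no new participants or data are needed. The downsides are a less favourable published figure and a between-group variance estimated from only seven groups, which will be imprecise.

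### The stated detectable difference of 0.23 SD does not follow from 96 completers per arm; the stated inputs give about 0.40 SD, and power at 0.23 SD is about 35%, not 80%

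*Protocol article*

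**What the plan says.** Section 2.2 of the protocol article contains the whole sample size argument in one paragraph. It randomises 120 people per arm and allows for dropout: "Expecting a 20% loss to follow-up between T0 and T1". It therefore expects "complete data from 96 participants in the intervention group and 96 participants in the control group of each large-scale pilot site", and it gives the total as 192. The assumptions are then listed: "We assumed equal standard deviations in the intervention group and the control group", together with "an alpha level of 0.05, and a power of 0.80". The paragraph says that, for this overall sample size and these assumptions, on the continuous outcomes "a difference of 0.23 SD (standard deviation) between the intervention group and the control group can be detected at follow-up".

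It does not say whether the test is one- or two-sided. It mentions no baseline-to-follow-up correlation, covariate adjustment, repeated-measures model or pooling of sites behind the 0.23.

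**The concern.** All the inputs needed to check the figure are in the same paragraph, and the difference is expressed in SD units, so no outside value is required. A trial with fewer than 100 people per arm cannot ordinarily detect a standardised difference as small as 0.23 with 80% power.

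This is the only power statement in the article. It covers the continuous outcomes, which would include the PROMIS-10 main outcome named in section 2.7. If it is wrong by a wide margin, a non-significant result could be taken as evidence against effects of 0.23 SD when the trial had roughly a one-in-three chance of detecting them. The Discussion (section 4) itself faults earlier studies for poor sample size calculation and low power, so readers will give weight to this number.

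**Working it through.** **Inputs, all from section 2.2:** 120 randomised per arm; 20% loss; equal SDs (SD set to 1); alpha 0.05; power 0.80; stated result 0.23 SD between groups at follow-up.

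**1. Dropout step.** 120 × 0.80 = 96 per arm and 2 × 96 = 192. This reproduces.

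**2. Detectable difference.** For two independent means with SD = 1,

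d = (z for alpha + z for power) × √(2/n).

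- √(2/96) = 0.1443.
- Two-sided: (1.960 + 0.842) × 0.1443 = 0.404 SD. The t-distribution gives 0.406 SD.
- One-sided: (1.645 + 0.842) × 0.1443 = 0.359 SD. The t-distribution gives 0.360 SD.

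The stated 0.23 SD is not reproduced. The ratio is 0.406 / 0.23 = 1.77.

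**3. Power at 0.23 SD with 96 per arm.**

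- Two-sided: Φ(0.23/0.1443 − 1.960) = Φ(−0.37) = 35.7% (t: 35.4%).
- One-sided: Φ(0.23/0.1443 − 1.645) = Φ(−0.05) = 48.0% (t: 47.7%).

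**4. Completers needed for 0.23 SD at 80% power, two-sided.** n = 2 × (2.802)² / 0.23² ≈ 297 per arm (298 with the t-distribution). At 20% loss, 297 / 0.80 gives 372 randomised per arm, against the planned 120.

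**5. Attempts to recover 0.23 from a slip with the stated numbers.**

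| Reading | Two-sided | One-sided |
|---|---|---|
| 120 per arm, dropout ignored | 0.362 | 0.321 |
| 192 taken as the per-arm size | 0.286 | 0.254 |
| Within-group test, n = 96 | 0.286 | 0.254 |
| Within-group test, n = 120 | 0.256 | 0.227 |
| 240 taken as the per-arm size | 0.256 | 0.227 |

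The two one-sided values of 0.227 come close, but each needs inputs that contradict the paragraph: one is not a between-group comparison, the other doubles the total trial size in each arm, and both ignore dropout.

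**6. Pooled sites.** With k sites of 96 per arm, three sites (288 per arm) give 2.802 × √(2/288) = 0.233 SD. Six sites give 0.165 and seven give 0.153.

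**7. Baseline adjustment (correlations are assumptions).** Adjusting T1 for T0 multiplies the detectable difference by √(1 − r²):

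| Assumed r | Detectable difference (two-sided) | Power at 0.23 SD |
|---|---|---|
| 0.5 | 0.35 SD | 45% |
| 0.6 | 0.32 SD | 51% |
| 0.7 | 0.29 SD | 61% |
| 0.8 | 0.24 SD | 76% |

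Setting 0.404 × √(1 − r²) = 0.23 gives r = 0.82. An analysis of change scores, with factor √(2(1 − r)), needs r = 0.84.

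**The case against.** The strongest defence is that the trial is a pre–post controlled design, so a baseline-adjusted or repeated-measures analysis may lie behind 0.23 SD, with its correlation given in a fuller document that is not shown. The requirement of r = 0.82 applies to a single follow-up. If both T1 and T2 were averaged and adjusted for T0, with the same correlation r between any two visits (an assumption), the factor becomes √((1 + r)/2 − r²). The detectable difference is then 0.286 SD at r = 0.5 and 0.243 SD at r = 0.7, and it reaches 0.23 SD at about r = 0.74. So a route to 0.23 SD exists. It does not support the sentence as printed, which lists its assumptions, names none of these, counts losses only from T0 to T1, and speaks of a between-group difference at follow-up.

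A second defence is that the figure belongs to the multi-site project. The words "96 participants in the control group of each large-scale pilot site" point that way, and three pooled sites come close. But the article names no three-site analysis; section 1 refers to seven countries and lists six sites, and pooling six or seven gives 0.165 or 0.153 SD. The origin is therefore unclear. If 0.23 SD is a pooled figure, it does not describe the Valencia comparison, which is the stated aim.

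A third point is that the practical harm is limited: the planned numbers and the dropout allowance agree with each other, and a confidence interval would show the real precision. That is fair, and enrolment is not affected. However, the 95% interval would have a half-width of about 1.960 × 0.1443 = 0.28 SD unadjusted, so even an observed difference of zero would not exclude 0.23 SD. That is the inference the printed sentence invites.

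**Conclusion.** The concern holds. On the inputs given in section 2.2, the detectable difference is about 0.40 SD (0.406 by the t-test) for a two-sided test and 0.36 SD for a one-sided test. Power at 0.23 SD is about 35% and 48% respectively, not 80%. The result rests on a two-sample comparison of means with equal SDs and 96 completers per arm, as the paragraph states; two-sided testing is assumed because sidedness is not given, and the figure fails either way. With baseline adjustment at assumed correlations of 0.5 to 0.7, the detectable difference is 0.35 to 0.29 SD, still above 0.23 SD. How 0.23 SD was obtained cannot be settled from the article.

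**What to change.** Replace the last sentence of the sample size paragraph with one that matches its inputs, for example: with 96 completers per arm, two-sided alpha 0.05 and power 0.80, a difference of 0.41 SD can be detected. State the sidedness.

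Remove the reference to each pilot site from this paragraph. If 0.23 SD belongs to an analysis pooling several sites, say which sites and how many participants, and attach the figure to that analysis only. If it rests on baseline adjustment or repeated measures, state the model and the assumed correlation.

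Specifying that the T1 comparison is adjusted for the T0 value would improve precision at no cost, since T0 is already collected and the article does not rule this out. The adjusted figure should then be reported with its assumption, for example 0.35 SD at r = 0.5.

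The cost is one corrected sentence and a less favourable stated figure. No extra participants or visits are needed.
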